### Setting

The project will take place at a national level in Jordan. Jordan is a middle-income country with limited resources allocated to mental health care. Specialist care for mental health problems is especially limited, with 1.04 psychiatrists, 2.97 mental health nurses, 0.11 psychologists, and 0.01 occupational therapists available per 100,000 people [35]. In addition, Jordan hosts the second most refugees per capita, globally, with the majority originating from Syria [36], further straining available mental health care. The majority of people residing in Jordan have access to the internet, with the World Bank reporting 83% of the population able to access the internet in 2021 [37] ensuring that a digital mental health intervention would be both accessible and scalable. The study will be implemented by the Institute for Family Health (IFH), a nongovernmental organization operating across Jordan.

### Participants and Recruitment

Participants will include youths aged 18 to 21 years residing in Jordan. Recruitment will be conducted through various means, including online advertisements and social media channels, adverts, and posters hosted in community centers, primary health care facilities, universities, and other areas frequented by this age group. During the recruitment process, potential participants will be able to access the study through either a QR code or a web link. Inclusion criteria for potential participants are (1) youths aged 18 to 21 years; (2) living in Jordan; (3) scores 20 or higher on the Kessler Psychological Distress Scale, 10-item version (K10) [38], indicative of moderate levels of psychological distress; and (4) having access to a device for intervention delivery or willingness to use one at a participating center. Exclusion criteria are (1) persons not between the ages of 18 and 21 years, and (2) imminent risk of suicide.

### Ethical Considerations

The RCT has been approved locally by the research committee of the School of Nursing, University of Jordan (PF.22.9 on March 23, 2022) and by the WHO ethics review committee (ERC; ERC.0003729 on July 1, 2022). Informed consent for participation in the trial will be taken prior to screening. Upon initially accessing the STARS website through the recruitment material, participants will receive information regarding the purpose of the study, an explanation of the assessments and study procedures, and information on the 2 interventions being trialed; STARS and EUC. This written information is additionally provided in a short, 3.5-minute animated video. They will subsequently be invited to complete the screening assessment. Participants will be remunerated JOD 4 (US $5.64) upon completion of the postassessment and again following the 3-month follow-up assessment.

### Study Procedures

Figure 1 presents a study flowchart outlining the study procedure. Prior to the commencement of the trial, STARS underwent a rigorous cultural adaption to ensure that the translation and material contained in STARS were relevant to the Jordanian context. This culturally adapted version of STARS was subsequently piloted in a feasibility RCT to ensure the safety, acceptability, and feasibility of the proposed research methodology (not yet published).

**Figure 1 figure1:**
[figure not shown]
Study flowchart. K10: Kessler Psychological Distress Scale, 10-item version; STARS: Scalable Technology for Adolescents and Youth to Reduce Stress.

Participants will be directed to take part in the screening procedure after accessing the online software tool, Qualtrics, through the research project’s website and reading through the study information outlined earlier. As part of the screening procedure, participants will first be asked their country of residence and age, administered the K10, and administered the screening questions for imminent risk of suicide. Participants outside of Jordan, not between the ages 18-21 years, or screening negative on the K10 will be informed that they are not eligible for participation and will be invited to contact the implementing team if they have any questions or would like to receive information on psychosocial services available close to them. If participants are excluded due to screening positive for imminent risk of suicide, a message will appear that they may need additional mental health support along with signposting to a nationally recognized helpline.

If participants meet all inclusion criteria, they will be invited to provide their contact information (phone number and/or email address). Immediately after having completed the screening or on the next working day, participants will be contacted by a member of the research team to answer any questions regarding the study. Participants will then receive a personalized link to the baseline questionnaires.

All subsequent assessments will also be completed remotely by participants either on their own private devices, or devices that will be made available in private rooms at the IFH health care centers. The baseline assessment will include the following instruments: Hopkins Symptoms Checklist, 25 (HSCL-25) [39], WHO Disability Assessment Schedule 2.0 (WHODAS 2.0) [40], WHO-5 Well-Being Index (WHO-5) [41], Psychological Outcomes Profile (PSYCHLOPS) [42], and the agency subscale of the State Hope Scale (SHS-A) [43]. In addition, participants will be asked about their previous mental health care use both related to services and prescribed medicines. Following the baseline assessment, participants will be randomized to either receive STARS or EUC.

The postintervention assessment is scheduled to take place at 8 weeks following baseline assessment completion for all participants. The postintervention assessment will include the HSCL-25, K-10, WHODAS 2.0, WHO-5, PSYCHLOPS, SHS-A, the Client Satisfaction Questionnaire adapted to internet-based interventions [44], and questions about whether they accessed mental health care during the trial. The final assessment will be conducted in 3 months following the postassessment, or 20 weeks after the baseline assessment, and will include the HSCL-25, K-10, WHODAS 2.0, WHO-5, PSYCHLOPS, SHS-A, and questions pertaining to any mental health services received between the postintervention assessment and the time of the 3-month assessment. Participants will receive up to 3 reminder messages and/or phone calls spread out over 2 weeks including their personalized link to the assessment. Participants will be remunerated JOD 4 (US $5.64) upon completion of the postassessment and again following the 3-month follow-up assessment. Table 1 presents a SPIRIT diagram outlining the assessment and intervention time points of the trial.

**Table 1 table1:** SPIRIT^a^: Schedule of enrollment, interventions, and assessments for the STARS^b^ trial.

		Measures	Enrollment (–T1)	Screening (T0)	Baseline (T1)	Intervention	Postassessment (T2; 8 weeks)	3-month follow-up (T3; 20 weeks)
**Enrollment**								
	Informed consent		✓					
	Eligibility screen			✓				
	Allocation				✓			
**Interventions**								
	STARS				✓	✓	✓	
	ETAU^c^				✓	✓	✓	
**Assessments**								
	Psychological distress	K10^d^		✓			✓	✓
	Depression symptoms	HSCL-25^e^			✓		✓	✓
	Depression symptoms	PHQ-2^f^				✓		
	Anxiety symptoms	HSCL-25			✓		✓	✓
	Functioning	WHODAS 2.0^g^			✓		✓	✓
	Subjective well-being	WHO-5^h^			✓		✓	✓
	Perceived problems	PSYCHLOPS^i^			✓		✓	✓
	Agency	SHS-A^j^			✓		✓	✓
	User satisfaction	CSQ-I^k^					✓	
	Mental health care use	2 items			✓		✓	✓

^a^SPIRIT: Standard Protocol Items: Recommendations for Intervention Trials.

^b^STARS: Scalable Technology for Adolescents and Youth to Reduce Stress.

^c^ETAU: enhanced treatment as usual.

^d^K10: Kessler Psychological Distress Scale, 10-item version.

^e^HSCL-25: Hopkins Symptoms Checklist, 25 subscales.

^f^PHQ-2: Patient Health Questionnaire, 2-item version.

^g^WHODAS 2.0: WHO Disability Assessment Schedule 2.0.

^h^WHO-5: WHO-5 Well-Being Index.

^i^PSYCHLOPS: Psychological Outcomes Profile.

^j^SHS-A: State Hope Scale, agency subscale.

^k^CSQ-I: Client Satisfaction Questionnaire adapted to internet-based interventions.

### Randomization and Blinding

Participants will be randomized to receive either STARS or EUC at a 1:1 allocation ratio following the baseline assessment. The randomization sequence will be developed through Qualtrics software and will be automated and embedded in the baseline questionnaire, with participants having their group allocation conveyed to them immediately upon completion of the assessment. Given the high proportion of Syrian refugees and other populations residing in Jordan, randomization will be stratified on a 1:1 ratio (Jordanian or Palestinian vs Syrian or other nationalities). Given that questionnaires are self-administered online, the outcome assessments will not be blinded.

### Interventions

#### Scalable Technology for Adolescents and Youth to Reduce Stress

The STARS intervention has been described in detail elsewhere [34]. The intervention is guided, brief, and consists of 10 chatbot sessions that have been developed from evidence-based techniques to address emotional distress experienced by youths. Participants are encouraged to complete 2 chatbot sessions a week spread out over 5 weeks, with each session taking approximately 20-25 minutes to complete. Upon completion of a chatbot session, the next chatbot session is unlocked immediately. During initial registration, participants will be able to opt-in to receive push notifications to receive reminders to complete prior chatbot sessions, to be alerted when a new session is available, and yet to be started, or when they have not accessed the intervention for some time. There are several notifications to improve engagement of participants with the chatbot. These notifications are described in Multimedia Appendix 3. The STARS intervention is being delivered using the OpenDialog automated conversation system.

Prior to use in this study, a cultural adaptation of the intervention took place to ensure that the chatbot was relevant to the Jordanian context (not yet published). As part of the cultural adaptation procedures, a prior iteration of the chatbot was translated from English to Arabic. This was then tested with youths using commonly used adaptation procedures outlined by WHO and detailed in a recently released manual [45]. These include techniques such as “cognitive interviewing,” a process that explores how relevant, understandable and acceptable an intervention is. Additionally, focus groups were used to understand the context and how to maximize the reach of STARS in Jordan. After the development of an updated STARS, there was an additional round of user testing to further refine the included content, with a focus on the wording and presentation of the content. The adapted version, called SALAM, will be used in this trial.

STARS was based on a cognitive behavioral therapy framework to deliver psychological content aimed at addressing the broad mental health needs reported by adolescents and youths. Cognitive behavioral therapy is recommended as an evidence-based mental health treatment for youths with emotional disorders according to WHO guidelines [20]. Lesson 1 (“Let’s get started”) provides participants with an overview of the intervention and an explanation of privacy and confidentiality. Lesson 2 (“Emotions are not our enemies”) provides participants with psychoeducation about emotions. Lessons 3 and 4 (“Breathe to relax”—parts 1 and 2) teach participants emotion regulation techniques, such as slow breathing. Lessons 5 and 6 (“What we do can change how we feel”—parts 1 and 2) focuses on behavioral activation. Session 7 (“Managing problems”) focuses on problem management techniques. Lessons 8 and 9 (“Talking kindly to yourself”—parts 1 and 2) teach participants about thought challenging. Finally, lesson 10 (“Put your skills together”) is focused on consolidating learnings and relapse prevention [34]. The techniques are taught by SALAM that sends brief text messages to which participants can respond using predefined response options consisting of prewritten text and emojis. The use of the response buttons is “practiced” during the first lesson. In some lessons, there is an opportunity to give a free-text response, for example, when participants are asked to specify a goal for the intervention that has not been predefined by the chatbot. Additionally, useful tools such as audio and video demonstrations (eg, breathing techniques, problem management) and practice quizzes will be available for use anytime, as will the ability to go back to a previous session. This can be done by navigating to the “session menu” where participants can select the lesson they would like to repeat. Throughout the intervention, users will be encouraged to practice and apply these skills in their day-to-day lives.

The training and materials for the guided component of the chatbot intervention are based on a guided self-help approach developed by WHO and used in several studies [17,18,46]. It consists of 5 weekly telephone calls by trained, nonspecialist e-helpers. The support calls last approximately 15 minutes each to provide participants with support and guidance to implement the STARS intervention techniques and to use the STARS intervention chatbot. E-helper support is strongly protocolized and outlined session-by-session for each support phone call in an e-helper manual. E-helpers are trained on the STARS intervention and research protocols during a 5-day training delivered by IFH. The training includes knowledge about psychological distress and other mental health problems, communication skills, providing support, responding to distress, and procedures for adverse events (AEs) including referral procedures. E-helpers can monitor their participants’ progress through the OpenDialog system and can view some of the participants’ responses. These are limited to specific parts that are relevant for the e-helper, such as responses to the mood check, the goal a participant selected, and free-text fields. Free-text responses will be monitored on a daily basis for any indications that the participant is unsafe (eg, in case a participant expresses suicidal ideation in a free-text field or suggests a harmful goal to work on in the intervention). E-helpers will be supervised on a weekly basis by a clinical supervisor based at IFH, with additional support to the project team from WHO. Clinical group supervision will ensure fidelity of the e-helper support calls, discussion of challenging situations when providing telephone support, and e-helper self-care. The clinical supervisor will also listen to 5% of e-helper support calls to provide feedback on the delivery of the support calls.

To evaluate treatment fidelity, a random sample (5%) of e-helper support calls will be audio recorded. Participants will be asked for verbal consent prior to recording. Recordings will be evaluated according to a treatment fidelity checklist. This information has also been added to the consent form.

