### Sample Size

A total of 344 participants will be included in the RCT. This sample size calculation was based on the results of prior trials exploring the effectiveness of comparable digital interventions which report effect sizes (Cohen *d*) ranging from 0.48 to 0.56 [17,18,59]. In addition, a similar effect size was used to determine the sample size for a similar RCT observing the effectiveness of a WHO-developed digital health intervention, based on a conservative, yet clinically significant effect size of 0.5 [60]. Assuming an effect size of 0.5 at a 3-month follow-up (power=90%; α=0.05, 2-sided), the trial would require 172 participants (STARS=86 and EUC=86). Given the high attrition rates reported in digital intervention studies, a conservative attrition rate of 50% was assumed. This attrition rate was informed by the results of the feasibility RCT and comparisons with protocols for similarly designed studies.

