### Statistical Analysis

To measure baseline differences between the 2 treatment arms, 2-tailed *t* tests will be conducted for continuous variables and chi-square tests for categorical data. To determine the effectiveness of the STARS intervention, intention-to-treat analysis will be conducted to compare the mean difference between STARS and EUC at baseline, post intervention, and 3-month follow-up. Differential change over time between treatment arms will be assessed using linear mixed models that accommodate missing data at subsequent assessments and provide differential slopes of trajectories between conditions. Hierarchical linear models study treatment effects because this allows the number of observations to vary between participants and handles missing data by using maximum likelihood estimation methods. Missing data will be assumed to be random if participants retained and not retained at 3 months do not differ on baseline characteristics. Fixed (intervention and time of assessment) effects and their interactions will be entered in unstructured models to yield indices of the relative effects of the treatments; time of assessment included baseline, post treatment, and 3-month follow-up. Analyses will focus on the primary outcome and secondary measures, with the main outcome time point being the 3-month follow-up relative to baseline. A subsequent per protocol completers analysis will be conducted, only including those who completed the 3-month follow-up, in order to assess the robustness of the primary analysis.

In addition to these analyses, the role of potential moderators and mediators, such as agency, on outcomes will be explored independently using the PROCESS macro. Two-tailed tests with a significance level of *P*<.05 will be reported for all analyses.

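### STARS participants share e-helpers and EUC participants do not, but the sample size makes no allowance for this and the described model names no e-helper term

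*Protocol article*

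**What the plan says.** All references are to the Methods of the protocol article.

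- **Interventions, STARS.** The chatbot comes with human guidance: "It consists of 5 weekly telephone calls by trained, nonspecialist e-helpers", each call lasting about 15 minutes. The helpers appear to have caseloads: "E-helpers can monitor their participants’ progress through the OpenDialog system". The number of helpers, the caseload and the rule for assigning participants to helpers are not given.
- **Interventions, Enhanced Usual Care.** Psychoeducation and a list of services are delivered through a website. No helper is described.
- **Sample Size.** "Assuming an effect size of 0.5 at a 3-month follow-up" ("power=90%; α=0.05, 2-sided"), the article arrives at 172 participants, 86 per arm. It adds that "a conservative attrition rate of 50% was assumed", which gives 344 randomized. No ICC or design effect appears.
- **Statistical Analysis.** "Fixed (intervention and time of assessment) effects and their interactions will be entered in unstructured models". The hierarchical model is justified by the varying number of observations per participant and by its handling of missing data. E-helpers are not mentioned.

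**The concern.** Individual randomization does not make outcomes independent when one arm is treated by a small number of people. If some e-helpers are more effective than others, participants of the same helper will resemble each other after treatment. An unstructured covariance over the three assessments captures correlation within a participant. It cannot absorb correlation between different participants of the same helper.

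Two things are at stake, and they belong to different analyses:

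- If the helper level is ignored, the confidence interval for the primary effect is too narrow and the type I error is above 5%.
- If the helper level is modelled, the interval is valid, but power at 86 per arm falls below the stated 90%.

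Both depend on an ICC above zero. The result matters beyond this trial, because the article ties open-access release of the intervention to the results of this trial and a second one.

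**Working it through.** **1. Reproduce the plan's figure.** Inputs from Sample Size: d = 0.5, two-sided α = 0.05, power 90%, attrition 50%.

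- Noncentral t for two independent groups: power is 0.8999 at 85 per arm and 0.9032 at 86 per arm. The smallest n reaching 90% is therefore 86 per arm, or 172 in total.
- Attrition: 172 / (1 − 0.5) = 344.

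Both figures match exactly, so the calculation is arithmetically right and contains no allowance for clustering.

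**2. Assumptions not in the document.** Number of helpers k = 4 to 12; ICC = 0.01 to 0.05; 86 analysed per arm; equal caseloads; total variance 1 in both arms; a single comparison at the 3-month follow-up; normal approximation.

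**3. Formulas.**

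- STARS design effect: DE = 1 + (86/k − 1) × ICC. EUC design effect: 1.
- True variance of the difference divided by model variance: R = (DE + 1)/2. True SE / model SE = √R. Understatement of the model SE = 1 − 1/√R.
- Type I error of the unadjusted test: 2 × [1 − Φ(1.96/√R)].
- Standardized effect under independence: 0.5/√(2/86) = 3.279. Power of a test using the correct SE: Φ(3.279/√R − 1.96). With R = 1 this is 90.6%, the normal-approximation counterpart of the 90.3% in step 1.

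**4. Worked case: 4 helpers, ICC 0.05.** DE = 1 + (21.5 − 1) × 0.05 = 2.025. R = 1.5125 and √R = 1.230. The true SE is 23% larger than the model SE; put the other way, the model SE is understated by 1 − 1/1.230 = 18.7%. Type I error = 2 × [1 − Φ(1.594)] = 11.1%. Adjusted power = Φ(2.666 − 1.96) = 76.0%.

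**5. Results over the assumed range.**

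| Helpers | ICC | DE | True SE / model SE | Type I error, unadjusted test | Power, adjusted test |
|---|---|---|---|---|---|
| 12 | 0.01 | 1.06 | 1.015 | 5.4% | 89.8% |
| 8 | 0.01 | 1.10 | 1.024 | 5.6% | 89.3% |
| 6 | 0.02 | 1.27 | 1.065 | 6.6% | 86.9% |
| 8 | 0.05 | 1.49 | 1.115 | 7.9% | 83.6% |
| 4 | 0.05 | 2.03 | 1.230 | 11.1% | 76.0% |

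The last two columns describe different analyses and should not be read as a pair. Under d = 0.5 the unadjusted test rejects with probability Φ((3.279 − 1.96)/√R), which is 90.3% in the top row and 85.8% in the bottom row. It keeps more apparent power only because its type I error is too high.

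**6. Does better retention remove the problem?** Suppose all 172 STARS participants are analysed, with 6 helpers and ICC 0.02. Then DE = 1 + (28.67 − 1) × 0.02 = 1.553, R = 1.277 and √R = 1.130. Adjusted power is 98%, but the unadjusted type I error rises to 8.3% because analysed caseloads are larger. The generous attrition allowance may rescue power; it does not rescue an unadjusted test.

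**The case against.** The strongest reply is that nothing shows the ICC to be above zero. The chatbot teaches the techniques, in 10 sessions of 20 to 25 minutes (200 to 250 minutes), against about 5 × 15 = 75 minutes of calls. Calls follow a session-by-session manual; helpers share a 5-day training and weekly group supervision, and a sample of calls is checked for fidelity. Outcomes are self-reported online, and the primary time point is 20 weeks after baseline, well after the 5-week support period. This stands as a reason to expect a small ICC. It gives no basis for assuming zero, and the training, supervision and fidelity checks show that the investigators regard helper delivery as something that can vary.

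A second reply is that the article lists fixed effects but does not give a full list of random effects, and an analysis plan that is not shown could include an e-helper term. That also stands. The firmest part of the point is therefore the sample size, whose 90% holds only without helper clustering whatever a later plan adds. For the model, one can say only that the description, followed as written, ignores the helper level.

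A reader might infer that the STARS standard errors are definitely too small, or that the sample size was miscalculated. The documents support neither. The first requires a positive ICC, and the second is contradicted by the exact reproduction. Nor does the article say that one helper makes all five calls to a participant; stable caseloads are inferred from its reference to helpers' own participants.

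**Conclusion.** The point holds conditionally. The plan describes helper contact in one arm only, sizes the trial as if all observations were independent, and names no helper term in the model. If the e-helper ICC is above zero, the unadjusted interval will be too narrow and a clustering-adjusted test will fall short of 90% power at 86 per arm.

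The size cannot be fixed from the document. It ranges from negligible (12 helpers, ICC 0.01) to material (4 helpers, ICC 0.05), and the upper end needs both unfavourable assumptions at once. With ICC = 0 nothing changes. The adjusted-power figures use a normal critical value, so with few helpers and small-sample degrees of freedom the true power would be somewhat lower. This is an inexpensive improvement worth making, not an error that invalidates the design.

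**What to change.** - Keep e-helper ID in the analysis dataset, including any change of helper for a participant.
- Before any analysis (the Results section says none had been done), specify a partially nested model: a random e-helper effect in STARS only, at the post-intervention and 3-month assessments, with EUC participants as singletons and Satterthwaite or Kenward-Roger degrees of freedom. Make it the primary analysis, or at least a prespecified sensitivity analysis.
- Report the number of helpers and the estimated ICC.
- State in the sample-size section that the 90% power assumes no e-helper clustering.

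The cost is one variable, which should already exist operationally because helpers follow their own participants in the delivery system, and one model term. Recruitment, treatment and assessments are unchanged. The downside is a somewhat wider interval and, if helpers are few, an imprecise ICC; in that case the sensitivity analysis should be read together with its uncertainty.
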